### Recruitment and visits

Recruitment will be assisted by advertising (not mentioning spa therapy) in the local press and by posting information in local pharmacies, physicians’ offices or clinics. In the case of recruitment difficulties, local companies known to have high rates of workers on sick leave for low back pain may be contacted. Following the advertising campaign, telephone contact between responding, potential study participants and a clinical research technician (CRT) will result in referral to a recruiting investigator (depending on location), who is responsible for obtaining consent and for enrolment, baseline evaluations and randomisation. The enrolment visit will start with an initial presentation and provision of informed consent for the UCHE intervention (Table 3). Following presentation of the “back book” and baseline evaluations, participants will be randomised and those allocated to the experimental arm will be invited to sign an additional consent form for spa therapy. As no biological collections or ancillary studies are foreseen in this protocol, further consent procedures beyond the latter are not required. Appointments will be made for spa therapy (in the next 60 days (maximum) for patients consenting to spa therapy in the experimental arm) and for follow-up visits with evaluating physicians for all patients in both arms at months 1, 6 and 12. The specific assessments required at baseline and during follow-up visits are detailed in Table 3 and closely follow the study outcomes plus the following: demographic data and disease history at baseline, home exercise observance and any required harms reporting. No specific post-trial care (beyond routine care) is foreseen.

### Promoting participant retention and completeness of follow up

Continued contact between study CRTs and patients is encouraged. Patients are requested to contact the study CRT in the case of visit unavailability or other problems. Conversely, the study CRTs will be contacting patients during the week preceding follow-up visits to provide a visit reminder and/or rescheduling as required.

### Harms

Few prospective studies have sought to evaluate the adverse effects and complications that may occur during a spa treatment [42–45]. Due to the absence of control groups, imputability is often not established and few studies clearly describe side effects. Among patients undergoing spa therapy, with or without radon, Franke et al. [39] observed: an increase in pain (7/1), hypertension (2/1), fatigue (2/1) or coloration of the skin and nails (2/0). Gáti et al. [46] observed three cases of respiratory tract infection, one case of cardiac arrhythmia, hypertension and cardiac decompensation, one case of cystitis and one case of gastroenteritis in relation to spa therapy. Another study reports a complete absence of adverse effects [37]. In other publications, adverse effects are not discussed. Based on adverse event reports from the largest studies [47, 48], no serious adverse events are expected. Based on the adverse effects observed during spa treatment for knee osteoarthritis, and in epidemiological studies, we expect to observe benign infections of the upper airways, increased pain or potentially leg erysipelas. A rarer but theoretically possible effect is the occurrence of opportunistic pulmonary infections (legionella) - a few cases and case series were described in the 1980s. These infections have become rare following a change in water disinfection methods in the spa centers [49].

Additional events that may be expected because they are associated with physical exercise in general are respiratory disorders and shortness of breath, cardiovascular disorders (chest pain, myocardial infarction, cardiac arrhythmia, tachycardia, vagal discomfort, hypotension or hypertension, fatigue and injuries (cramps, muscle aches, sprains, strains, tears, fractures)).

Harms reporting will be carried out in compliance with the French regulations in force (or their equivalent in other countries as appropriate) throughout the study (see Table 3). There is no anticipated harm or compensation for trial participation.

### Statistics

Statistical analyses will be performed by the Department of Medical Information at the University Hospitals of Montpellier, Montpellier, France, using the R programming environment [50] or SAS (enterprise guide V.7.1 or higher). An intention-to-treat structure will be implemented. The intention-to-treat population will include all randomised patients and will respect their allocations, regardless of whether or not they started the allocated interventions. Analyses may be adjusted according to clinical or inclusion criteria to take into account population heterogeneity. Though generally presented here, a more detailed statistical analysis plan will be drafted prior to the end of participant inclusion (and made available at https://osf.io/ahpwy/).

Descriptive statistics (for the total population and for each arm) will be provided as means with standard deviations for quantitative variables with normal distributions according to the Shapiro-Wilks test, or as medians with interquartile variables for other quantitative variables. Numbers and percentages will be provided for categorical variables.

As indicated in Table 4, the primary analysis is the comparison of the proportion of patients with a clinically relevant change in pain at 6 months; this will involve the uncorrected chi square (χ^2^) test for independent groups, or alternatively Fisher’s exact test if the conditions for the χ^2^ test are not met. We expect to perform an interim analysis of the number of patients in both groups with clinically relevant improvement as soon as there are 100 patients suitable for analysis with 6 months of follow up. The purpose of the latter is to assess futility, and a difference between arms (intervention – control) < 0 will stop the trial.

As concerns secondary analyses, comparisons of qualitative variables will be performed in the same manner as for the primary analysis. The centrality of quantitative variables will be compared between arms using parametric (*t* test) or non-parametric (Mann Whitney test) analysis for independent groups, as appropriate. For longitudinal data, the preferred method will employ mixed models with patients set as a random effect and study arm as a fixed effect; an appropriate interaction term (group × time) will be used to detect differences between study arms in the rate of change. In addition, a medico-economic analysis comparing the two patient management strategies will be conducted according to international [51] and French recommendations [52]. A cost-utility analysis will be carried out, with utility values evaluated using the EQ-5D-5 L. The following direct medical costs will be considered: hospitalizations and consultations, transport, drugs and laboratory assessments.

Variables that are used for stratification (spa or presence of a professional activity) may be used in sub-group analyses. Covariate-interaction tests are the preferred method for detecting sub-group differences [53]. Statistical analyses will be adjusted on variables found to be imbalanced between arms. Sub-group tests will be considered as exploratory in nature.

The general hypothesis of the study supposes more improvement in the experimental arm as compared to the control arm. A difference will be considered statistically significant when the type I error rate is less than or equal to 0.05. As concerns missing data, patients lost to follow up will not be considered as withdrawn from the study but will be analysed as failures for the primary endpoint. Any deviations from the statistical analysis plan must be authorized by the study methodologist and will be thoroughly documented and justified in the study analysis report.

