### Study setting and population

This study will take place in and around well-established spa centres in Europe (see Table 1). Patients living within a 30-km radius of a participating spa centre and meeting eligibility criteria (Table 2) may participate. Recruitment, enrolment and follow-up visits will occur outside of spa centres (and independent thereof) in participating private offices/clinics, public general hospitals and public university hospitals. The single-payer system in France, where most of the participating spa centres are located, offers medical care to all citizens and residents, and the study population should thus represent a wide range of socioeconomic and rural versus urban backgrounds.

**Table 1 Tab1:** Participating spa centres

Name	Nearby city, Country
Aix-les-Bains	Chambéry, France
Amnéville	Metz, France
Balaruc les Bains	Montpellier, France
Dax	Bayonne, France
Evico Terme	Trentino, Italy
Greoux les Bains	Aix en Provence, France
Hervideros de Cofrentes	Valencia, Spain
Jonzac	Bordeaux, France
Royat	Clermont Ferrand, France
Russian Research Center for Medical Rehabilitation and Balneology	Moscow, Russian Federation
Saint Amand les Eaux	Valenciennes, France
Saint Paul lès Dax	Bayonne, France
Saline Cacica	Northeast Romania
Széchenyi Bath	Budapest, Hungary

**Table 2 Tab2:** Inclusion and exclusion criteria for participants

Inclusion criteria	Exclusion criteria
Adult patient presenting with chronic low back pain: usual pain of the lumbar region lasting for more than 3 months. This pain may radiate to the buttocks, iliac crest, and does not go past the knee [7]	Patients with specific low back pain
Patient presenting upon inclusion with a current pain intensity on a visual analogue scale (VAS) > or = 40 mm.	Patients with severe depression, psychosis
The patient has signed the informed consent form	Patients who have already had a spa treatment in the previous 6 months
Subject aged over 18 and under 80 (years)	Patients with a contraindication for spa treatment^a^
The patient is a beneficiary of a social security programme (national health insurance)	Patients with a professional activity related to balneotherapy (to avoid any conflict of interest)
	Patients with cruralgia or sciatic pain beyond the knee
	Other treatments that may interact according to the investigator’s judgement
	Patients who live more than 30 km away from the spa^b^

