**Blinding success**						
Guess-the-group question for evaluators						✓

*D* day, *M* month, *W* week, *FABQ* Fear, Avoidance, Belief Questionnaire, *EQ-5D-5L* Euroqol Group 5 dimension, 5 level questionnaire

^a^Enrolment visits are performed by recruiting investigators, who are not the same as evaluating investigators

^b^Follow-up visits are performed by evaluating investigators, who are not the same as recruiting investigators

^c^Or just after the end of spa therapy, if applicable

^d^The patient will also be provided with a practical guide on how to manage back pain (the “back book”), including a recommended home exercise programme [15]

^e^Age, sex, duration of current episode of low back pain, signs of spread of osteoarthritis, pain spreading, history of lumbar surgery, need for frequent position changes, bad mood and irritability, sleep disorders due to back pain

^f^Semi quantitative scales that reflect (1) the patient’s and, separately, (2) the physician’s overall opinion concerning the patient’s state of health

^g^Resource use including infiltrations, hospitalizations, physical treatments (massages, traction, physical therapy) and medical imaging of the lumber spine will be tracked

^h^Costs will be estimated using resource-use data gathered during visits and the French National Cost Scale. Indemnities related to days of sick leave will be included in cost estimates

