### Allocation and blinding

Following initial consent covering the UCHE intervention and subsequent baseline assessments, patients will be randomly assigned to either control or experimental groups in a 1:1 allocation ratio (Fig. 1, Table 3). In line with a single Zelen design [23, 24], patients randomised to the experimental group will be informed about the additional spa therapy intervention and invited to sign an additional consent form; furthermore, these patients can refuse spa therapy, but statistical analysis will be performed on an intention-to-treat basis. Patients allocated to the control group have already consented to the UCHE intervention and will proceed without information on spa therapy; this design is necessary to avoid bias associated with “resentful demoralisation” effects [24].

Allocation is performed using a computer-generated randomisation schedule and stratified by the recruiting investigator/spa (the latter are paired, but separate) and by whether or not the patient has a professional activity. Baseline evaluations and the subsequent randomisation are performed by the recruiting investigators through specific modules administered via a password-protected Internet-accessible electronic case report form (eCRF). The randomisation module will become accessible to investigators only after key elements of baseline data have been entered in the eCRF.

To blind the study as much as possible, follow-up assessments are performed during specific follow-up visits (see Table 3) by an “evaluating” physician, who is different from the “recruiting” investigator. Every attempt will be made to keep evaluating investigators blinded. Specifically, study participants will be instructed to not mention study participation or spa therapy to their evaluating physicians (at the end of the final follow-up visit, the study clinical research associate (CRA) will ask the evaluator a guess-the-group question in order to evaluate the success of blinding). As concerns follow-up care, emergency situations requiring specific unblinding procedures are not foreseen in this protocol. Finally, the statisticians will be blinded, i.e. study arms will be referred to as “A” or “B” when the database is presented for analysis. Unveiling of the study arms will occur after completion of planned statistical analyses.

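### The primary chi-square ignores the randomisation strata (valid but conservative if they predict response), and a loosely placed rule adjusts for whatever turns out imbalanced

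*Protocol article*

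**What the plan says.** - **Design.** Under Allocation and blinding, randomisation is "stratified by the recruiting investigator/spa (the latter are paired, but separate) and by whether or not the patient has a professional activity". Table 1 lists 14 spas.
- **Primary test.** The Statistics section names one test for the responder proportion, for "pain at 6 months; this will involve the uncorrected chi square" test for independent groups, with Fisher's exact test as fallback. Table 4, note b, says the same.
- **Use of the strata in analysis.** The only stated use is optional: "Variables that are used for stratification (spa or presence of a professional activity) may be used in sub-group analyses".
- **Adjustment.** Two sentences in Statistics bear on it. One is discretionary: "Analyses may be adjusted according to clinical or inclusion criteria to take into account population heterogeneity". The other is directive: "Statistical analyses will be adjusted on variables found to be imbalanced between arms". The second stands in the sub-group paragraph, between the preference for interaction tests and the statement that sub-group tests are exploratory. It names no variable list, threshold or model.

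**The concern.** Two things are at stake.

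**Precision.** Stratified allocation removes most of the between-stratum variation from the treatment difference. An unstratified chi-square still counts that variation in its variance, so if spa or working status predicts response the standard error is too large. The strata may well matter here: the spas lie in several countries, each may add treatments by local consensus, and the Background names spa-specific effects and effects in working patients as secondary objectives.

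**Choice of covariates.** After proper randomisation, imbalance is chance. A rule that adjusts for what is found imbalanced selects covariates by that chance and not by their relation to outcome. It will also seldom select spa or activity, because stratification tends to balance them. A chi-square test cannot adjust for anything, so if the rule applies to the primary endpoint there are two candidate primary results and no statement of which one counts.

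**Working it through.** **1. The plan's own figure.** Inputs from Sample size: 40% v 25%, alpha 4% (two-sided assumed), power 80%, so z = 2.054 and 0.842.
- Pooled formula: [2.054·√(2·0.325·0.675) + 0.842·√(0.24 + 0.1875)]² / 0.15² = 162.2, so 163 per arm and 326 in total.
- Unpooled formula: (2.054 + 0.842)²·0.4275 / 0.0225 = 159.3, so 160 per arm and 320 in total.
- Arcsine formula: 324 in total.

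The stated 322 lies within this range, and 322/0.9 = 357.8 gives 358. The sample size therefore rests on an ordinary unstratified comparison.

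**2. Number of strata.** 14 spas × 2 activity levels = 28, or 322/28 = 11.5 patients each if equal. The number of recruiting investigators per spa is not given, so there may be more and smaller strata.

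**3. Why the chi-square is conservative.** The overall variance p(1−p) is the within-stratum part plus Var(p_s), the variance of the stratum response rates. With balance within strata, only the first part affects the treatment difference. For logit-scale stratum SD τ, Var(p_s) ≈ [τ·p(1−p)]², so the surplus share is about τ²·p(1−p). With p = 0.25 under the null:
- τ = 0.5: share 0.25 × 0.1875 = 0.047. The effective critical value is 2.054/√0.953 = 2.104, giving a type I error of about 3.5%.
- τ = 0.8: share 0.64 × 0.1875 = 0.12. The critical value is 2.054/√0.88 = 2.189, giving about 2.9%.

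**4. Simulation.** N = 322, alpha 4%, 28 strata of equal expected size, blocks of 4, marginal rates held at 40% v 25%, 20,000 runs per cell. The Monte Carlo standard error is about 0.3 points for power and 0.14 for type I error. Block size, equal strata and τ are assumptions; the article gives none of them.

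| τ | Chi-square type I | Chi-square power | Mantel-Haenszel power | Gain (points) |
|---|---|---|---|---|
| 0 | 3.8% | 80.7% | 80.2% | −0.5 |
| 0.3 | 4.1% | 79.6% | 79.7% | 0.1 |
| 0.5 | 3.4% | 80.3% | 81.4% | 1.1 |
| 0.8 | 3.1% | 81.1% | 84.1% | 3.0 |
| 1.0 | 2.7% | 81.5% | 86.0% | 4.5 |

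Mantel-Haenszel type I error stayed at 3.8 to 4.1%. A second simulation of the same design gave gains of about 0, 1.5, 3 and 4 points at SD ≤0.3, 0.5, 0.8 and 1.0, with chi-square type I error of about 2.6 to 3.5% for SDs of 0.5 to 1.0.

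**5. The imbalance rule.** Table 3, note e, lists nine items, beginning "Age, sex, duration of current episode of low back pain, signs of spread of osteoarthritis, pain spreading, history of lumbar surgery". At an assumed p<0.05 trigger and independence, P(at least one flagged) = 1 − 0.95⁹ = 0.37; simulation gave 0.37 to 0.38.

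A second exercise compared models: nine covariates, N = 322, alpha 4%, 3,000 runs, standard error about 0.8 points for power and 0.4 for type I error. The conditional odds ratio was held fixed, so absolute power falls as the covariates strengthen; compare within rows only.

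| Total covariate log-odds SD | Power: unadjusted | Power: triggered | Power: always adjusted | Type I: triggered | Type I: best of the three |
|---|---|---|---|---|---|
| 0.5 | 76.1% | 76.0% | 77.5% | 4.5% | 5.7% |
| 0.8 | 71.8% | 72.3% | 77.4% | 3.5% | 5.6% |
| 1.2 | 61.1% | 60.6% | 71.0% | 3.4% | 6.2% |

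Triggered adjustment recovers almost none of the power that advance adjustment would, and its own type I error is not clearly above 4%.

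**The case against.** The primary test is named in advance, twice, and it is valid. The article describes its methods as general and promises a more detailed analysis plan before inclusion ends. Statisticians see the arms only as A and B until planned analyses are done, and deviations need authorisation and documentation. The imbalance sentence stands among sub-group matters and may be meant only for them. The precision gain depends on between-stratum variation that the article does not report, and the chi-square's power stays at about the planned 80% throughout.

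Most of this stands and limits the point:
- A reader might infer that the primary model is left open until the data are seen. The text does not support that: the test is fixed, and the imbalance sentence reaches it only through its general wording.
- A reader might infer that planned power is lost. It is not: 322 reproduces without any credit for stratification.
- A reader might count some 20 baseline measures and quote 1 − 0.95²⁰ = 64%. That treats correlated pain, disability and drug measures as independent, and applies a p<0.05 trigger that the article does not state.

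The promised analysis plan does not remove what remains. The article itself states both an unstratified test and an imbalance trigger, and gives the strata only an optional sub-group role. Masked arm labels do not settle which model is primary.

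**Conclusion.** The point holds as one of efficiency and clear specification, not validity. The unstratified chi-square controls type I error, on the conservative side when the strata are prognostic. Using the strata would gain about 0 power points at a stratum SD of 0.3 or less and about 1 to 4.5 points at SDs of 0.5 to 1.0. This assumes about 28 equal strata, and the SDs are not given in the article.

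The imbalance rule is a poor way to choose covariates and, if it applies to the primary endpoint, contradicts the named test. A reader might also infer that it inflates the false-positive rate. The calculations do not show that: type I error was 3.4 to 4.5% against a nominal 4%, and rose to 5.6 to 6.2% only when the most favourable of three models was picked after the fact, which the plan does not propose. The change is worth making because it costs little; the trial does not fail without it.

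**What to change.** - Make the primary analysis a Mantel-Haenszel test and risk difference stratified by spa and professional activity, with a rule set in advance for pooling small spas. Alternatively, use a logistic model with a random spa intercept, professional activity and baseline VAS, all fixed in advance, reported as a standardised risk difference.
- Keep the chi-square as a supportive analysis.
- Delete the sentence that triggers adjustment on observed imbalance. Name any further covariate before outcome data by arm are seen.

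Cost: wording only. Spa and activity are already used at randomisation, baseline VAS is already collected, and the sample size need not change. The downside is sparse strata, which need the pooling rule or the random intercept; one fixed effect per stratum in ordinary logistic regression should be avoided. If the strata turn out not to be prognostic, there is no gain, and at τ = 0 the simulated Mantel-Haenszel power was 0.5 points lower.

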The composition of the spa therapy intervention is based on previous results in the domain. Massage [16–21], heat therapy [20] and water exercises [22] have all been demonstrated as helpful for low back pain. Water exercises in particular have similar efficacy to regular exercise regimens, and are sometimes better tolerated [22]. For the present study, the spa therapy intervention consists of 18 consecutive days of spa therapy (3 weeks of treatment, excepting Sundays), that must occur within 60 days of randomisation (Table 3). The latter will always combine mineral water with physical and hydrotherapeutic treatments, including massages, heat and water exercises: (1) pool activities will be carried out by qualified and trained physiotherapists. Small patient groups (limited to 8–15 patients at a time) will participate in pool sessions with 10 min of free bathing and 15 min of supervised exercises in water at 35 °C; (2) underwater massages on painful areas will be performed by qualified and trained physiotherapists in 10-min sessions with water jets at a temperature of 38 °C; (3) mud applications at a temperature of 45 °C will be performed in 15-min sessions, and will include all painful areas (even outside the lumbar region if necessary). In addition to the latter three criteria, further treatments may be added by consensus of spa practitioners in each spa centre. Patients randomised to the spa therapy arm will be invited by the recruiting investigator to keep trial participation and spa therapy a secret from evaluating investigators. Their participation in spa therapy (observance) will be recorded by spa centre staff.

If required, treatment-stopping for home-exercises will be decided via collaboration between the patient and his/her evaluating doctor. Treatment-stopping may occur for spa-therapy in case of an adverse event, is decided on a case-by-case basis by the on-site doctors overseeing spa-therapy, and does not result in study exclusion.

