The EQ-5D-5L questionnaire [30, 31] will be used to track changes in quality of life. This self-administered questionnaire consists of two pages: the first contains the EQ-5D descriptive system and the second a visual analogue scale. The descriptive system has 5 dimensions (mobility, self-care, usual activities, pain/discomfort, anxiety/depression), each described by 5 levels of intensity (“no problems”, “slight problems”, “moderate problems”, “severe problems” and “extreme problems or complete inability”). The respondent must indicate one intensity level for each dimension	Repeated measures at baseline and 1, 6 and 12 months Proportion of patients with clinically relevant changes according to van der Roer et al. [32] at 1, 6 and 12 months	Mixed model for longitudinal data^c^ Comparison of distributions^b^
Patient Acceptable Symptom State (PASS): yes/no response to the following question: “If you take into account all the activities you have in your daily life, the importance of your pain and your disability, do you consider your condition as satisfactory?” [33]	Proportion of patients with patient-acceptable symptoms at baseline and 1, 6 and 12 months	Comparison of distributions^b^
Overall opinion of the patient on his/her state of health (5-point Likert scale)	Proportion of patients in each state at baseline and 1, 6 and 12 months	Comparison of distributions^b^
Overall opinion of the evaluating physician on the patient’s state of health (5-point Likert scale)		
Daily drug consumption over the past 72 h: • Analgesics (in milligrammes of paracetamol and morphine equivalents) • NSAIDs (reported in milligrammes and as a percentage of the maximum dose) [34] • Corticosteroids (in milligrammes equivalent prednisone) • Benzodiazepine muscle relaxants: % of maximum dose	Repeated measures at baseline and 1, 6 and 12 months	Mixed model for longitudinal data^c^
Number of infiltrations (epidural, posterior articular)	Centrality for the cumulative number of infiltrations at 12 months	Comparison of centrality^d^
Estimated per-patient cost for 1 year of care (based on observations of health resource use throughout the study: drug consumption, hospitalizations, imaging)	Centrality for the cumulative cost of care at 12 months	Comparison of centrality^d^

^a^ The primary outcome

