^b^ The comparison of the number of patients improved (or other proportion) will be performed via distribution comparison tests for independent groups (either the uncorrected χ^2^ test, or Fisher’s exact test if the conditions for the χ^2^ test are not met)

^c^ A mixed model with patients as a random effect and study arm as a fixed effect will be used. A significant time × group interaction would indicate differences in the speed of recovery/change between groups

^d^ Means will be compared using the *t* test for independent groups when variable distributions are normal according to the Shapiro-Wilks test, or otherwise via the Mann Whitney test for comparing medians

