### Sample size

Data from two unpublished, open-label studies on typical patients receiving spa therapy indicate estimated rates of clinically relevant change in VAS pain scores of 47% (8/17) and 38% (10/26). Our hypothesis is that the proportion of patients experiencing improvement at 6 months will be 40% in the experimental arm (UCHE plus spa treatment) versus 25% in the control arm (UCHE only). Considering a type 1 risk level set at 4% (1% will be used for an interim analysis following the inclusion of the first 100 patients) and a type 2 risk level set at 20% (i.e. statistical power of 80%), the minimum sample size required is 322 participants. To maintain power for analysis on observed data and expecting a drop-out rate of approximately 10%, this estimate is increased to a total of 358 paricipants (179 per study arm).

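### Two 5-point opinion scales are tested without using their order, and the group × time term is read as speed of change although spa is a single early course

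*Protocol article*

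**What the plan says.** **Longitudinal outcomes.** Table 4 assigns pain VAS, RMDQ, FABQ, EQ-5D-5L and drug consumption, each measured at baseline and months 1, 6 and 12, to a mixed model with patient as random effect and study arm as fixed effect. The Statistics section states that the group × time term "will be used to detect differences between study arms in the rate of change". Footnote c of Table 4 says that a significant interaction "would indicate differences in the speed of recovery/change between groups". Neither place says whether time is linear or categorical.

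**Treatment timing.** Under Interventions and study arms, spa is 18 treatment days "that must occur within 60 days of randomisation". Table 3 puts the first follow-up visit at days 28 to 60, or just after spa ends.

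**Opinion scales.** For the patient's and the evaluating physician's overall opinion, both 5-point Likert scales, the metric in Table 4 is "Proportion of patients in each state at baseline and 1, 6 and 12 months". Footnote b makes the test an uncorrected chi-square, or Fisher's exact test where chi-square conditions fail.

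**The concern.** *Opinion scales.* A chi-square or Fisher test on a 2 × 5 table gives the same result if the five columns are shuffled. It spreads its power over 4 degrees of freedom, whereas the question is whether one arm sits higher on an ordered scale. A real shift is then more easily reported as no difference.

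*Longitudinal outcomes.* The Background expects greater improvement with spa, the Statistics section supposes more improvement in the experimental arm, and the Discussion justifies the 12-month follow-up by durability. All three call for the size of the between-arm difference at given visits. The stated meaning of the interaction is a speed. With one early course, a natural pattern is a difference that is present at the first follow-up visit and then persists or fades. A single slope over 0, 1, 6 and 12 months describes that poorly and can have the wrong sign when spa is better at every follow-up visit.

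**Working it through.** **1. The plan's own figure.** The Sample size section uses 40% versus 25%, type I risk 4%, power 80% and 1:1 allocation. With two-sided alpha and unpooled variance, n per arm = (2.054 + 0.842)² × (0.40×0.60 + 0.25×0.75) / 0.15² ≈ 8.38 × 19 ≈ 159.3, so 160 per arm and 320 in total. The pooled-variance formula gives 163 per arm, 326 in total. The stated 322 lies between them, and 322/0.9 = 357.8 gives the stated 358. So 161 per arm is used below, with two-sided alpha 0.05 for secondary outcomes (the article gives 0.05 without stating sidedness).

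The documents give no effect sizes, SD, correlations or Likert distributions for these outcomes. All such values below are assumptions.

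**2. Opinion scales.** Take control proportions of 10/20/40/20/10% and a proportional-odds shift of 1.75, which gives 6.0/13.7/37.5/26.6/16.3% in the other arm.

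- Chi-square: noncentrality = n Σ(p₁−p₀)²/(p₁+p₀) = 7.58. With 4 df and critical value 9.49, power is 57.8% (57.1% in 4,000 simulations).
- Rank-sum: ln(1.75) × √(322 × 0.25 × 0.9217 / 3) = 0.560 × 4.973 = 2.78, where 0.9217 = 1 − Σp̄³. Power = Φ(2.78 − 1.96) ≈ 79% (78.3% in simulation).

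Simulated ranges over three control distributions (symmetric, uniform, skewed):

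| Odds ratio | Chi-square | Rank-sum | Loss within the same distribution (points) |
|---|---|---|---|
| 1.5 | 32–34% | 51–54% | 19–20 |
| 1.75 | 57–61% | 78–81% | 20–21 |
| 2.0 | 79–80% | 93–94% | 13–14 |

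**3. Group × time, early effect that fades.** Assume spa-minus-control differences of 0/−12/−8/−4 mm at months 0/1/6/12, SD 22 mm and correlation 0.5 (random intercept).

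- Linear time: mean time is 4.75, Sxx = 90.75 and Sxy = +6.0, so the slope difference is +0.066 mm/month, against spa. SE = √(2 × 22² × 0.5 / (161 × 90.75)) = 0.182, z = 0.36 and power 6.5%, of which about 1% is in favour of spa.
- Visit as a factor: noncentrality = 161 / (2 × 22² × 0.5) × Σ(d−d̄)² = 0.3326 × 80 = 26.6. With 3 df, power is 99.6%.
- Baseline-adjusted month-6 difference: SE = √(2 × 22² × 0.75 / 161) = 2.12, z = 3.77 and power 96%.

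**4. Other patterns.** Differences in SD units at months 1/6/12; power at correlations 0.3 / 0.5 / 0.7:

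| Pattern | Linear time | Visit as factor |
|---|---|---|
| Sustained 0.33 | 42.3 / 55.1 / 76.9% | 73.2 / 87.5 / 98.5% |
| Fading 0.50/0.33/0.16 | 6.3 / 6.9 / 8.2% | 93.5 / 98.7 / >99% |
| Growing linearly to 0.33 | 80.2 / 91.4 / 99.0% | 64.8 / 80.6 / 96.3% |

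**The case against.** On the longitudinal half the main reply is strong. Linear time is never stated: the text asks only for a suitable interaction term, and Table 4 lists four fixed visits. With visit as a factor and baseline among the outcomes, the same term is a valid and powerful test of treatment effect, so the low power comes from a coding that the article does not fix. The fading pattern is also one that nearly cancels a slope. A persistent −10 mm effect gives 82% even with linear time, and differences of 0/−4/−8/−12 mm give 99.9%. Arm is a fixed effect too, and averaged over the four visits its difference in the fading case (−24/4 = −6 mm) has 87% power. Finally, coding of time and visit contrasts are ordinary content of the detailed analysis plan that the article announces.

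All of this stands against reading the article as committing to a straight-line analysis. A reader might also infer that the month-6 difference would go unestimated. That is not supported: a group × visit model yields it directly, and the Statistics section also provides t or Mann-Whitney comparisons between arms. What remains is the stated interpretation, given in two places, which does not match the hypothesis however time is coded. A 3-df interaction result should not be reported as a difference in speed, and by itself it gives neither a direction nor a month-6 estimate.

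On the opinion scales, chi-square has correct type I error, tests the metric that Table 4 names, and can detect non-monotone differences that a rank test would miss. The reported proportions will show direction even though the test does not. So it would go too far to call the test invalid or to say that power is lost for nothing in return. The loss for an ordered shift stands.

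**Conclusion.** The point on the opinion scales holds as stated: the test is fixed in Table 4, is valid, and is inefficient for an ordered shift by about 13 to 21 power points at 161 per arm, for assumed proportional odds ratios of 1.5 to 2.

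The point on the longitudinal outcomes holds as a fault of stated interpretation, with a conditional consequence. If the speed wording is carried out with linear time, power for an early, fading benefit can fall to about 6%; with visit as a factor it stays above 99% in the same scenario. Nothing in the article shows that the linear version will be used, so the 6% is a risk to close off and not a property of the plan.

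Type I error is correct in both parts. It might be inferred that the trial's main conclusion is exposed. It is not: the 6-month responder comparison is binary, its chi-square test fits it, and its sample size reproduces.

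**What to change.** - **Opinion scales:** keep reporting the proportion in each state, but test both outcomes with a proportional-odds model or a Wilcoxon rank-sum test, stratified if wished. The cost is less sensitivity to non-monotone differences.
- **Longitudinal outcomes:** in the Statistics section and in footnote c of Table 4, replace the rate and speed wording. State that visit is a categorical factor and that the reported effects are baseline-adjusted between-arm differences at months 1, 6 and 12, with month 6 as the key contrast. The cost is a few more parameters, and some power if the effect truly grew linearly (for example 80.6% against 91.4% at correlation 0.5).

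Both are changes of wording in the protocol and analysis plan. They need no new data, visits or patients.
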